### Interventions

Frozen-thawed embryo transfer will be performed in NC with spontaneous ovulation. Transvaginal ultrasonography (TVUS) is used to monitor follicular development and endometrial growth. In the late follicular phase, that is, on days 8–12 of the cycle (depending on the length of the patient’s menstrual cycle), when the dominant follicle develops to a mean diameter of more than 14 mm, serum LH level is monitored every other day until the LH surge appeared (21). When the endometrial thickness reaches more than 8 mm and the endometrium is classified as type A or B, embryo transfer is performed 4 days (D3 embryos) or 6 days (D5/D6 blastocysts) after the appearance of the LH surge. If luteinization of unruptured follicles occurs, embryo transfer is canceled. Plasma hCG levels were measured 14 days after embryo transfer.

Patients in the LPS group are given P_4_ sustained-release gel Crinone ^®^ 8% (Crinone, Merck Serono, Switzerland) vaginally, 90 mg/time, once a day and P_4_ injection (Zhejiang Xianju Pharmaceutical Co., Ltd., Zhejiang, China) intramuscularly, 20 mg/vial, twice a day until 14 days after FET (21). For pregnant women, LPS treatment should be continued until 10 weeks of gestation.

### Data collection

Relevant treatment data of patients are collected at the corresponding time points: (1) basic data (2–4 days of menstruation); (2) dominant follicle development to an average diameter of more than 14 mm to the day of ovulation under TVUS monitoring; (3) D3 embryo transfer day (ovulation day + 4 days); (4) blastocyst transfer day (ovulation day + 6 days); (5) pregnancy test day (embryo transfer day + 14 days). In the case of pregnancy and delivery, data will be collected from the patient’s medical records as well as the birth records of the newborn for registration of obstetric and neonatal outcomes up to 1 year after delivery. Any protocol deviations or unanticipated effects on the conduct of the trial will be registered. All study personnel will be trained in data collection and entry, handling of data discrepancies, and procedures performed during study visits. Data collection forms are available by contacting the study steering committee.

### Blood sample collection

As part of the basic data stage, follicle-stimulating hormone (FSH), LH, estradiol (E_2_), and P_4_ should be measured, followed by LH, E_2_, and P_4_ until an LH surge occurs. E_2_ and P_4_ should be measured on the day of embryo transfer, and E_2_, P_4_, and β-hCG should be measured on the day of pregnancy test.

### Research biobank and biobank for future research projects

In addition to samples for serial analysis, a total of 12 ml of blood samples (serum, and plasma) will be drawn at each sampling time and stored in a -20°/-80° freezer at Rigs Hospitalet. Samples will be identified by anonymous subject ID numbers to maintain subject confidentiality. In this study, the sample can be used as a backup of continuous analytical samples or stored in a biological sample bank for possible future research projects. Patients will be asked to sign a separate informed consent form to store the blood samples in a biobank for future research. Additional approval from the Ethics Committee will be required for future projects. If samples are not used, they will be destroyed according to the biomaterial destruction rules after the end of the study or no later than 5 years after the last patient is enrolled.

### Transvaginal ultrasound

During FET cycles, Transvaginal ultrasonography is required as per clinical routine. Transvaginal ultrasonography is used to determine endometrial thickness and antral follicle number on days 2–5 of menstruation in a treatment cycle. Endometrial thickness and the size of the dominant follicle are estimated in the late follicular phase, i.e., on days 8–12 of the cycle depending on the length of the patient’s menstrual cycle. TVUS was repeated until the dominant follicle reached more than 17–18 mm and an LH surge appeared. If conception occurs, an early pregnancy scan will be performed at pregnancy 7–8 to assess fetal viability and crown-rump length.

### Data management

According to the informed consent form signed by all study participants, the study staff and relevant regulatory authorities can directly access the relevant data of patients to study and follow up the relevant conditions of patients and facilitate the quality control. All data for the study will be uploaded into electronic case report forms in the study’s electronic data capture system for ease of data integration and management. The study electronic data capture system had a complete audit trail based on anonymous subject identification numbers used in the study. The system will interval program numeric data to detect possible input errors in the study. This platform is protected by a password-protected access system. The system will automatically backup data daily and store it on the server. Documents containing patient identifying information will be stored separately in a document with limited access. Source documents will be reviewed by Good Clinical Practice-trained study personnel (not participating in the study) to ensure completeness and accuracy of the data. The reviewer will assess the overall quality of the data and confirm that the site meets the protocol requirements. Data will be processed in accordance with the Data Protection Act and approved by the Data Review Center. The principal study site will develop a unified data processing agreement form with other cooperative centers and strictly implement it.

### Data sharing plan

Study data will be shared according to International Committee of Medical Journal Editors guidelines. Data sharing may occur with parties who provide the purpose associated with the detailed use of data. The other party’s study must obtain the corresponding study approval. The study data will not be shared with the same team as the purpose of this study. Data sharing will take place 3 months after the publication of papers involving the study’s primary and secondary outcomes. Any new research project must be conducted under the premise of approval. The party requesting data sharing will be charged accordingly.

### Outcome measures

#### Primary outcome

The primary outcome is OPR. Ongoing pregnancy is defined as intrauterine pregnancy confirmed by TVUS examination at more than 12 weeks of gestation accompanied by normal fetal heart beats.

#### Secondary outcomes

(1) Positive pregnancy: positive pregnancy refers to serum β-hCG ≥ 10 mIU/ml 14 days after embryo transfer; (2) Embryo implantation rate: the number of gestational sacs determined by TVUS examination divided by the total number of embryos transferred; (3) Pregnancy loss: pregnancy loss refers to the loss of an intrauterine pregnancy that is less than 28 weeks gestational age; (4) Ectopic pregnancy: ectopic pregnancy refers to the implantation and development of embryos in sites other than the uterine coelom; (5) Multiple pregnancy: multiple pregnancy refers to the simultaneous presence of two or more fetuses in the uterine cavity; (6) Live birth: live birth refers to newborns with gestational age at delivery ≥ 24 weeks and heartbeat and respiration; (7) Pregnancy-related complications: including preeclampsia, gestational hypertension, cesarean section, and postpartum hemorrhage (>1,000 ml); (8) Obstetric complications: including gestational diabetes (GD), placental pathology (accreta, previa), specify spontaneous preterm birth or induced preterm birth; macrosomia; small for gestational age, large for gestational age; low birth weight: [absolute weight, relative weight compared to mean at specific gestational local reference curve (*p* or Z-value)], and perinatal death.

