### Eligibility criteria

#### Inclusion criteria

Having regular ovulatory cycle; at least one embryo or blastocyst available for transfer.

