### Study population and recruitment

The study population include patients undergoing elective freeze-all strategy following IVF/ICSI cycles. Morphological evaluation of cleavage-stage embryos and blastocysts will be performed according to the Racowsky et al. **(19)** and the Gardner Scoring System **(20),** respectively. At least one grade I or II embryo with D3 blastomeres > 6 or high-quality blastocysts with a score ≥ 3BB will be cryopreserved. The investigators will contact all patients interested and eligible for the study by telephone. Patients interested in participating in the study will visit the corresponding reproductive center on days 2–4 of the menstrual cycle, after having fully understood the content of the study. Here, they further understand the details of the study and sign an informed consent. Each individual may be included only once and only in the first FET cycle after the oocyte retrieval. All medical personnel in the study will receive all necessary information and training to uniformly handle patients at each reproductive center. All sites staff have sufficient experience in conducting clinical trials.

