### Randomization

Randomization will be performed by an independent statistician using a computer-generated randomization schedule with block randomization (block size of four) stratified by female age (< or ≥ 35 years) at LH-surge day in NC-FET cycle. Patients will be randomized in a 1:1 ratio to one of the following groups: (i) LPS group: Patients will receive vaginal combined intramuscular P_4_ treatment starting on the day of ovulation. (ii) Non-LPS group: Neither LPS nor any other therapies are administered to patients.

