### Statistical analysis and interpretation of data

The intention-to-treat (ITT) analysis includes both dropout and cancelation cycles. The per-protocol (PP) analysis includes all patients who strictly followed the study protocol. In the as-treated analysis, patients who subsequently received LPS but not NC-FET are excluded, however, those who subsequently received LPS from NC-FET until 10 weeks of gestation are included. We measured OPRs and identified differences between groups based on relative risk (RR) and 95 confidence interval (CI). PP analyses will be also performed for all reproductive outcomes.

Continuous data were compared using Student’s *t*-test and results are presented as mean (standard deviation, SD) or median (inter-quartile range, IQR). Categorical data with expected frequencies less than five is assessed using χ^2^ analysis and Fisher’s exact test. *P*-values less than 0.05 is considered statistically significant. Data analysis will be performed using SPSS 26.0 and R 4.1.3. Multivariate logistic regression analysis will be performed to identify variables independently associated with OPR.

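### Implantation rate is counted per embryo while women are randomised, and the tests named make no allowance for two embryos in one woman

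*Protocol article*

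**What the plan says.** Under Secondary outcomes, the protocol article defines implantation rate as "the number of gestational sacs determined by TVUS examination divided by the total number of embryos transferred". This is a pooled ratio with embryos in the denominator.

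The randomised unit is the woman. Under Randomization: "Patients will be randomized in a 1:1 ratio to one of the following groups". Under Study population and recruitment: "Each individual may be included only once and only in the first FET cycle after the oocyte retrieval". Each woman therefore contributes one transfer, and the only clustering possible is among embryos placed in that transfer.

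The number of embryos transferred is not stated. The inclusion criteria ask for "at least one embryo or blastocyst available for transfer", which is a minimum and not a cap. The Interventions section allows cleavage-stage embryos or blastocysts and gives no number.

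The section on statistical analysis names four methods:
- Continuous data: "Continuous data were compared using Student", that is, the t-test.
- Categorical data: "Categorical data with expected frequencies less than five is assessed using" chi-square and Fisher's exact test.
- Ongoing pregnancy rate (OPR): relative risk with a 95% confidence interval.
- OPR again: multivariate logistic regression.

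P-values below 0.05 count as significant. No method is linked by name to implantation rate, and none is described as allowing for several embryos in one woman.

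**The concern.** Two embryos placed in the same woman share her endometrium, her age and her assigned treatment, so their results are likely to be positively correlated. A chi-square test on the pooled counts would treat each embryo as a separate independent observation and credit the trial with more information than it has. The standard error behind the test would be too small, and a difference in implantation between luteal support and no support would be declared significant too often.

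What is at stake is one secondary comparison. It is still a direct efficacy contrast between the arms, and a falsely significant implantation result could colour how the OPR result is read.

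**Working it through.** **The plan's own figure.** The only sample size stated is for OPR: 50% in both arms, margin 10 percentage points, one-sided alpha 0.05, power 90%.

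n per arm = (1.6449 + 1.2816)² × 2 × 0.5 × 0.5 / 0.10² = 428.2, rounded up to 429. With 15% dropout, 429 / 0.85 = 504.7, so 505 per arm and 1,010 in total. All three figures reproduce. OPR is counted per woman, so nothing below alters them. The article gives no figure for implantation rate.

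**Inputs for the check**
- Per-embryo denominator, randomisation by woman, one cycle per woman, 0.05 threshold: from the article.
- q, the share of women receiving two embryos (the rest receive one): not in the article; assumed from 0 to 1.
- ICC, the correlation between two embryos in one woman: not in the article; assumed from 0 to 0.5.

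**Formulas**
- Design effect for the pooled ratio: DE = [(1 − q) + 2q(1 + ICC)] / [(1 − q) + 2q] = 1 + ICC × 2q / (1 + q).
- The true standard error is √DE times the naive one.
- Real two-sided error of a nominal 5% test = 2 × [1 − Φ(1.96 / √DE)].

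**Worked case, q = 1 and ICC = 0.3.** DE = 1 + 0.3 × 2/2 = 1.30; √1.30 = 1.140; 1.96 / 1.140 = 1.719; real error = 8.6%.

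| q | ICC | DE | SE ratio | Real error |
|---|---|---|---|---|
| 0 | any | 1.00 | 1.00 | 5.0% |
| any | 0 | 1.00 | 1.00 | 5.0% |
| 0.25 | 0.1 | 1.04 | 1.02 | 5.5% |
| 0.25 | 0.3 | 1.12 | 1.06 | 6.4% |
| 0.5 | 0.1 | 1.07 | 1.03 | 5.8% |
| 0.5 | 0.3 | 1.20 | 1.10 | 7.4% |
| 0.5 | 0.5 | 1.33 | 1.15 | 9.0% |
| 1 | 0.1 | 1.10 | 1.05 | 6.2% |
| 1 | 0.3 | 1.30 | 1.14 | 8.6% |
| 1 | 0.5 | 1.50 | 1.22 | 11.0% |

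**Simulation.** Beta-binomial data with 429 women per arm, an assumed implantation rate of 40% and 10,000 runs per setting gave these real errors:
- q = 1: 5.8% at ICC 0.1, 8.2% at ICC 0.3 and 11.3% at ICC 0.5.
- q = 0.5, ICC 0.2: 5.9%, against 6.6% by formula. This was the widest gap, and it closed in a longer run.
- q = 0: 5.5%, against 5.0% by formula. This gap also closed in the longer run.

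**The case against.** **The test is inferred.** This stands. The statistical section assigns no test to implantation rate. Read literally, its sentence on categorical data covers only tables with small expected counts, and the t-test would apply if a rate were formed for each woman. A reader might infer that the plan prescribes chi-square for this outcome; it does not. Still, the defined quantity is a pooled proportion and no per-woman rate is defined. The relative risk and the regression are stated for OPR. Chi-square/Fisher is therefore the most natural reading.

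**Multiple transfer is not shown.** This stands too. A reader might take it as established because multiple pregnancy is an outcome: "multiple pregnancy refers to the simultaneous presence of two or more fetuses in the uterine cavity". That is only suggestive, since one embryo can split. A denominator of total embryos does separate work mainly when some women receive more than one, but this also is a hint and not proof.

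**No interval is planned for this outcome.** Also correct. One might infer that the trial's confidence intervals will be too narrow, but the article specifies an interval only for OPR: "We measured OPRs and identified differences between groups based on relative risk (RR) and 95 confidence interval (CI"). The effect would appear in the implantation p-value.

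**This is detail for the analysis plan.** An analysis plan that is not shown may handle clustering. But the article does more than stay silent: it lists its between-group tests, and the listed tests do not suit the per-embryo outcome that it defines.

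**Conclusion.** The point holds in conditional form. As written, the most natural analysis of implantation rate is a per-embryo chi-square or Fisher test, which ignores that women were randomised. The p-value is too small only if some women receive two embryos and their results are positively correlated; the article settles neither.

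The range starts at no effect. It reaches 5.8% to 8.6% real error with half to all women receiving two embryos and ICC 0.1 to 0.3, and 9% to 11% at ICC 0.5. These sizes rest on assumed values of q and ICC.

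A reader might extend this to the trial's main conclusion. The documents do not support that: OPR is counted per woman, each woman enters once, and 429, 505 and 1,010 stand. The matter is a modest one, confined to one secondary comparison.

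**What to change.** Add one sentence to the section on statistical analysis: implantation rate will be compared between arms with the woman as the cluster, using the pooled ratio of sacs to embryos with cluster-robust standard errors under working independence, or a bootstrap that resamples women. Report the number of embryos transferred in each arm beside it.

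The choice of method matters in two ways. Working independence or the bootstrap keeps the point estimate exactly as defined, whereas GEE with an exchangeable correlation would reweight women when the number of embryos varies. A binary logistic model per embryo does not fit the numerator directly if one embryo yields two sacs; the pooled ratio has no such difficulty.

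The cost is a sentence of wording and, where transfers are not all single, a slightly larger p-value. R, which the article already names, can do either analysis. No new patients are needed, and the OPR analysis and sample size stay as they are. If every transfer proves to be single, the result is essentially unchanged.

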### Non-inferiority design and power calculation

The present study will adopt the non-inferiority design. Due to previous studies showing that NC-FET treated with LPS does not achieve the same outcome as NC-FET treated without LPS, and that treatment without LPS has the advantages of being less costly and less painful. Specifically, we assumed a 10% margin of non-inferiority and a 50% OPR in two arms based on our center’s experience with FET. The number of cases in each group was calculated at 429, according to the design of 1:1 parallel non-inferiority, the unilateral test with alpha = 0.05, and the power of 90%. Assuming a drop rate of 15%, there are 505 cases per group and 1,010 cases for the two groups.

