### Drop-outs and cancel cycles

Dropout refers to the study participants’ voluntary decision to withdraw from the study due to personal subjective factors. The canceled cycles were those who were forced to cancel the cycles due to endometrial lesions found in TVUS, failure of follicular development or failure of embryo thawing and resuscitation up to 21 days in the cycle. The researchers will make a detailed summary of the number and causes of dropout and cancelation in both groups and completion characteristics within and between groups. Based on our experience, the dropout rate will be up to 15%. If the actual dropout rate is higher than expected, we will discuss the potential bias, analyze the differences between the results and draw conclusions accordingly.

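### The sample size rests on a one-sided 5% test of a 10-point difference, but the only interval stated for the primary outcome is a 95% CI on the relative risk

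*Protocol article*

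**What the plan says.** Under Non-inferiority design and power calculation, the protocol article gives:

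- the margin and rates: "we assumed a 10% margin of non-inferiority and a 50% OPR in two arms";
- the error rate and power: "the unilateral test with alpha = 0.05, and the power of 90" per cent;
- the result: "The number of cases in each group was calculated at 429";
- the inflation: "Assuming a drop rate of 15%, there are 505 cases per group and 1,010 cases for the two groups".

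Under Statistical analysis and interpretation of data, differences in ongoing pregnancy rate (OPR) are assessed by "relative risk (RR) and 95 confidence interval (CI"). P-values below 0.05 count as significant, with no statement of one or two sides. That section does not mention the margin. The abstract names intention-to-treat (ITT) and per-protocol (PP) as the primary strategies. The ITT analysis keeps drop-outs and cancelled cycles; the PP analysis keeps only patients who strictly followed the protocol.

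Under Drop-outs and cancel cycles, "Dropout refers to the study participants’ voluntary decision to withdraw from the study due to personal subjective factors". Cancelled cycles are defined separately, and the 15% is again attached to drop-out.

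**The concern.** A one-sided 5% test corresponds to the lower limit of a two-sided 90% CI. The lower limit of a conventional two-sided 95% CI is a one-sided 2.5% test. The article uses the first to size the trial and gives an interval of the second kind for the primary outcome. It also changes scale: the sizing is on a difference in proportions, the interval on a ratio.

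Two things are at stake. First, the stated 90% power may not belong to the analysis that decides the trial. Second, the chance of wrongly declaring no luteal support non-inferior is 5% on the sizing text and 2.5% on the usual reading of the analysis text. A result whose 90% CI clears the margin and whose 95% CI does not could be called either way once the data are known. The Discussion expects the results to be usable in practice as soon as they are published, so the rule should be fixed beforehand.

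A smaller worry concerns the PP set. If the 15% covers voluntary withdrawal only, cancelled cycles come out of the 429 as well.

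**Working it through.** **Inputs.** OPR 50% in both arms (true difference 0), margin 0.10 read as an absolute difference, one-sided alpha 0.05, power 90%, 1:1 allocation, 15% drop-out: all from the power calculation section. The absolute reading of the margin is an inference, tested in step 2.

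**1. The plan's own figures.** n per arm = [p1(1−p1) + p2(1−p2)] × (z_alpha + z_beta)² / margin² = 0.5 × (1.645 + 1.282)² / 0.01 = 428.2 before rounding of the z-values, so 429. Inflation: 429 / 0.85 = 504.7, so 505 per arm and 1,010 in total. Both reproduce.

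**2. Which scale produced 429.** On log RR with 50% in both arms, the variance of log RR is 2(1−0.5)/(0.5n) = 2/n, so n = 2 × (z_alpha + z_beta)² / (ln RR margin)². An assumed margin of RR 0.80 (40% against 50%) gives about 344 per arm; an assumed RR 0.90 gives about 1,543. Neither is 429, so the sizing was on the risk difference.

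**3. Power on the risk-difference scale.** Power = Phi(0.10/SE − z), with SE = sqrt(0.5/n).

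| n per arm | SE | 0.10/SE | two-sided 90% CI (z = 1.645) | two-sided 95% CI (z = 1.960) |
|---|---|---|---|---|
| 429 | 0.0341 | 2.929 | 90.0% | 83.4% |
| 505 | 0.0315 | 3.178 | 93.7% | 88.8% |

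Simulating the lower Wald limit gave 83.9% and 89.1% for the 95% CI. If the 15% who drop out all count as not pregnant in the ITT analysis (assumption; OPR 0.85 × 50% = 42.5%), power at 505 is 89.5%.

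**4. Where the two rules disagree.** With 429 per arm, the 90% CI clears −0.10 when the observed difference is above −0.10 + 1.645 × 0.0341 = −0.044. The 95% CI needs −0.10 + 1.960 × 0.0341 = −0.033. An observed deficit of roughly 3.3 to 4.4 points is non-inferior by one rule and not by the other.

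**5. Power on the scale the analysis section names.** SE of log RR at 429 = sqrt(2/429) = 0.068. With a two-sided 95% CI:

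- assumed margin RR 0.80: Phi(0.223/0.0683 − 1.960) = about 90%;
- assumed margin RR 0.90: Phi(0.105/0.0683 − 1.960) = about 34%.

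The article gives no RR margin, so power on that scale is undetermined.

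**6. Cancelled cycles.** No cancellation rate is stated. If a further 5% to 15% of those randomised left the PP set (assumption), 505 × 0.80 = 404 to 505 × 0.70 = about 354 per arm would remain, and power with the 95% CI on the risk difference would be about 81% to 76%.

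**The case against.** The strongest reply is that the article never says non-inferiority will be concluded from the 95% CI. The analysis sentence describes how differences are assessed and contains no decision rule. The sidedness of the interval is not stated either: a one-sided 95% bound would agree exactly with the sizing, and P below 0.05 is compatible with a one-sided test. This is a condensed article, and a full analysis plan may set the rule. This stands to the extent that 83% is conditional. It does not remove the mismatch, because both the error rate and the interval are stated here and, read conventionally, they disagree.

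A reader might infer that the trial's power is really 83%, or that the sample size was miscalculated. The documents support neither. The 429 and 505 follow exactly from the stated inputs. The 83% needs a two-sided 95% CI, used as the decision rule, on the risk difference, in the 429 evaluable patients. The ITT set, which keeps drop-outs and cancelled cycles, has about 89%. On the RR scale that the analysis names, no power figure can be given.

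On cancelled cycles, a reader might infer a definite further loss of power. The size of any loss rests on an assumed rate and on when patients are randomised. Table 1 puts randomisation at baseline; the Randomization section can be read as placing it on the day of the LH surge. On the later timing, failed follicular development would mostly come before randomisation and not deplete the arms, although failure of embryo thawing would still come after it. The ITT set is unaffected in number.

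**Conclusion.** The point holds as a mismatch between two stated parts of the plan, not as an arithmetic error. The sizing uses a one-sided 5% test on the risk difference; the only interval for the primary outcome is a 95% CI on the relative risk.

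If the decision uses a two-sided 95% CI for the risk difference against a 10-point margin, power falls short of the stated 90% by about 7 points in the PP set (429 per arm) and about 1 point in the ITT set (505 per arm). This assumes 50% OPR in both arms and no true difference. The false-positive risk is open between 2.5% and 5% until one rule is stated.

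The cancelled-cycle point is secondary. The wording separates cancellation from the 15%, but the documents do not allow its effect to be sized.

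**What to change.** State one decision rule, before any comparative data are seen, on the risk-difference scale with the margin written as 10 percentage points. Report the RR as supportive. Then choose one of:

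- **Two-sided 95% CI (one-sided 0.025).** Restate power as about 83% for 429 evaluable per arm and about 89% for all 505.
- **Two-sided 90% CI (one-sided 0.05).** The 90% power at 429 stands, and the 95% CI is labelled descriptive only.

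In the drop-out section, state that the 15% allowance covers voluntary withdrawals and cancelled cycles together for the PP set, and reconcile the time of randomisation between Table 1 and the Randomization section.

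The cost is a few sentences. The first option makes the stated power less favourable; the second accepts the higher false-positive risk openly. Neither adds patients. For reference only, holding 90% power with the 95% CI would need 0.5 × (1.960 + 1.282)² / 0.01 = 525.4, so 526 evaluable per arm; 526 / 0.85 gives 619 per arm and 1,238 in total. The fix does not require this.
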